## Abstract

**Introduction:**

Recent evidence suggests that larger blood pressure reductions and multiple antihypertensive drugs may be harmful in older people, particularly frail individuals with polypharmacy and multimorbidity. However, there is a lack of evidence to support deprescribing of antihypertensives, which limits the practice of medication reduction in routine clinical care. The aim of this trial is to examine whether antihypertensive medication reduction is possible in older patients without significant changes in blood pressure control at follow-up.

**Methods and analysis:**

This trial will use a primary care-based, open-label, randomised controlled trial design. A total of 540 participants will be recruited, aged ≥80 years, with systolic blood pressure <150 mm Hg and receiving ≥2 antihypertensive medications. Participants will have no compelling indication for medication continuation and will be considered to potentially benefit from medication reduction due to existing polypharmacy, comorbidity and frailty. Following a baseline appointment, individuals will be randomised to a strategy of medication reduction (intervention) with optional self-monitoring or usual care (control). Those in the intervention group will have one antihypertensive medication stopped. The primary outcome will be to determine if a reduction in medication can achieve a proportion of participants with clinically safe blood pressure levels at 12-week follow-up (defined as a systolic blood pressure <150 mm Hg), which is non-inferior (within 10%) to that achieved by the usual care group. Qualitative interviews will be used to understand the barriers and facilitators to medication reduction. The study will use economic modelling to predict the long-term effects of any observed changes in blood pressure and quality of life.

**Ethics and dissemination:**

The protocol, informed consent form, participant information sheet and all other participant facing material have been approved by the Research Ethics Committee (South Central—Oxford A; ref 16/SC/0628), Medicines and Healthcare products Regulatory Agency (ref 21584/0371/001–0001), host institution(s) and Health Research Authority. All research outputs will be published in peer-reviewed journals and presented at national and international conferences.

**Trial registration number:**

EudraCT 2016-004236-38; ISRCTN97503221; Pre-results.

Strengths and limitations of this studyThis will be the first UK randomised controlled trial to compare a strategy of antihypertensive medication reduction with usual care in primary care.The pragmatic trial design, with broad inclusion criteria, will make findings of the study externally valid in routine clinical practice.Allowing the attending general practitioner to choose the medication to be reduced will maximise external validity of the trial results, but precludes the possibility of blinding the participants and investigators.The trial will be powered to detect a non-inferior difference in blood pressure control at follow-up, but not necessarily secondary outcomes such as differences in rates of cardiovascular disease, adverse events and quality of life.

## Introduction

The general population is ageing^1^ and, consequently, the number of people living with age-related chronic conditions is increasing.^2^ Hypertension is the number one comorbid condition in older people with multiple chronic conditions^3^ and 52% of those aged ≥80 years are prescribed two or more antihypertensive drugs (equivalent to approximately 1.25 million people in the UK).^4^ Blood pressure lowering has been shown to be effective at preventing stroke and cardiovascular disease in healthy individuals aged ≥80 years with stage 2 hypertension (systolic blood pressure of >160 mm Hg) and high-risk stage 1 hypertension.^5 6^ However, as with many trials,^7 8^ these studies included healthier populations with lower polypharmacy and multimorbidity than might be expected in the general elderly population. In addition, there is evidence to suggest that larger blood pressure reductions and multiple antihypertensive prescriptions may be harmful in older people.^9 10^ Evidence from observational studies also suggests that higher intensity blood pressure treatment is associated with increased risk of falls in older people,^11^ although this is also disputed.^5^

Some patients consider the increased risk of falls and other adverse events (AEs) to be as important as the risk of myocardial infarction or stroke, particularly those taking medications for primary prevention of cardiovascular disease.^12^ Thus, decisions over blood pressure lowering in the elderly, particularly the frail elderly, require the weighing of harms and quality of life. However, clinicians can often struggle to stop prescribing medication due to a perceived lack of evidence, fear of the reaction of other prescribers, fear of precipitating events such as stroke or angina and concern that patients will feel their care is being cut.^13 14^

There is limited evidence from randomised trials examining the safety of antihypertensive medication reduction or withdrawal.^15–19^ The Hypertension in the Very Elderly Trial (HYVET)^5^ enrolled some patients on antihypertensive treatment who were then randomised to placebo (effectively complete medication withdrawal) and the second Australian National Blood Pressure trial investigators followed up participants who withdrew medication during the trial run-in period but who were not randomised into the trial. They found younger patients with lower baseline blood pressure and fewer drug prescriptions were more likely to sustain medication withdrawal at 12-month follow-up.^20 21^ However, there are few trials comparing a specified strategy of antihypertensive medication reduction with usual care in terms of effects on blood pressure control and quality of life.^17^ In addition, there are no previous economic modelling studies of a strategy of medication reduction in the elderly.

The aim of this work will be to examine whether antihypertensive medication reduction in patients with controlled systolic hypertension (≤150 mm Hg) who are being prescribed two or more antihypertensives is possible without significant changes in blood pressure control at follow-up.

## Methods

### Aims and outcomes

The aim of this study is to determine whether antihypertensive medications can be safely reduced without systolic blood pressure increasing beyond what is clinical acceptable at follow-up.

The primary outcome is the proportion of participants with clinically acceptable blood pressure levels at 12-week follow-up (defined as a systolic blood pressure <150 mm Hg). Secondary outcomes will examine:The proportion of participants in the intervention arm who maintain medication reduction through to follow-up (ie, are *not* restarted on therapy).The difference in quality of life (according to EQ-5D-5L) between groups at 12-week follow-up.The difference in frailty (according to the frailty index)^22^ between the two groups at 12-week follow-up.The difference in the change in mean clinic systolic blood pressure (from baseline) between the two groups at 12-week follow-up.The difference in reported side effects to medication between the two groups at 12-week follow-up (including coughs, dizziness, syncope, and ankle swelling).The difference in routinely reported serious adverse events (SAEs) between the two groups at 12-week follow-up (hospitalisation due to falls, myocardial infarction, stroke or all-cause mortality).

### Design

This trial will use a primary care-based, open-label, randomised controlled, two-parallel groups, non-inferiority trial design, recruiting 540 participants with controlled blood pressure (systolic <150 mm Hg) on two or more antihypertensive treatments. Participants will be randomised to a strategy of medication reduction (intervention) or usual care (control) and followed-up for 12 weeks (figure 1). Embedded qualitative and economic analyses will examine barriers and facilitators to medication reduction and the cost-effectiveness of the approach.

**Figure 1 F1:**
[figure not shown]
Trial flow diagram. *Monitoring of blood pressure at home will be encouraged but those not willing or able will still be included in the trial. All participants will be asked to attend a safety monitoring visit with their GP/nurse 4 weeks after baseline. GP, general practitioner; BP, blood pressure; HDL, high-density lipoprotein; ICD, International Statistical Classification of Diseases and Related Health Problems; CVD, cardiovascular disease; eGFR, estimated glomerular filtration rate; MARS, Medication Adherence Rating Scale; MOCA, Montreal Cognitive Assessment.

### Trial participants

Patients eligible for the trial will be aged ≥80 years, with systolic blood pressure <150 mm Hg (current UK guideline recommendation)^23^ receiving ≥2 antihypertensive medications. They will have no compelling indication for medication continuation and in the opinion of the attending GP, may potentially benefit from medication reduction due to existing polypharmacy, comorbidity and/or frailty (box 1).Box 1Trial inclusion and exclusion criteria
**Inclusion criteria**
Participant is willing and able to give informed consent for participation in the trial.Male or female, aged 80 years or above.Clinic systolic blood pressure <150 mm Hg (according to screening measurement at baseline—clinic blood pressure defined as the mean of the second and third readings taken at 1 min intervals).Prescribed two or more antihypertensive medications to lower blood pressure for at least 12 months prior to trial entry. Antihypertensive medications defined as any ACE inhibitor, angiotensin II receptor blocker, calcium channel blocker, thiazide and thiazide-like diuretic, potassium-sparing diuretic, alpha-blocker, beta-blocker, vasodilator antihypertensives, centrally acting antihypertensives, direct renin inhibitors, adrenergic neuron blocking drugs or loop diuretics.Stable dose of antihypertensive medications for at least 4 weeks prior to trial entry.In the investigator’s opinion, could potentially benefit from medication reduction due to existing polypharmacy, comorbidity, non-adherence or dislike of medicines and/or frailty.In the investigator’s opinion, is able and willing to comply with all trial requirements.
**Exclusion criteria**
A participant has heart failure due to LVSD and is on only ACE inhibitors/ARBs and/or beta-blockers and/or spironolactone (removing any of which would be contraindicated).A participant has heart failure but has not had an echocardiogram since its onset (might have undiagnosed LVSD and a compelling need for ACE inhibitors/ARB and beta-blockers).Investigator deems that there is a compelling indication for antihypertensive medication continuation.Any other significant disease or disorder which, in the opinion of the investigator, may either put the participants at risk because of participation in the trial, or may influence the result of the trial, or the participant’s ability to participate in the trial (eg, terminal illness, house bound and unable to attend baseline and follow-up clinics).Suffered a myocardial infarction or stroke within the past 12 months.Blood pressure being managed outside of primary care.Unable to provide consent due to incapacity.A participant with secondary hypertension or previous accelerated or malignant hypertension.Participants who have participated in another research trial involving antihypertensive medication in the past 4 weeks.ARB, angiotensin II receptor blocker; LVSD, left ventricular systolic dysfunction.

Participants will be identified and recruited from general practices via the UK Clinical Research Network. Potentially eligible patients will be identified by trained practice staff searching practice-based electronic disease registers using a standardised strategy. GPs will be asked to check the search results and remove people whom they believe to be unsuitable to participate in the study. Remaining potentially eligible patients will be sent letters of invitation from their GP and those expressing an interest in the trial will be asked to attend a screening and baseline appointment. Patients not responding to the first invitation will receive one reminder letter (up to 4 weeks after the first letter). Other potentially eligible patients may also be approached opportunistically by a member of the clinical care team. Those who do not wish to take part will be asked to fill in a short questionnaire detailing their reasons.

### Baseline visit

Eligible patients will have informed consent taken by the GP. During the consent appointment, the GP will show a 2 min study video infographic (see online supplementary material) and go through the participant information sheet explaining the exact nature of the trial. Having had a chance to ask questions, those individuals willing to participate will give written informed consent by means of a participant dated signature and dated signature of the GP who presented and obtained the informed consent.

10.1136/bmjopen-2018-022930.supp1Supplementary data

Some participants will be invited to have their interview audio-recorded for qualitative analysis during their study visits. Those who are interested will be asked to sign a response slip prior to meeting the GP. Consent to audio-recordings will not have a bearing on an individual’s care or eligibility for the main trial.

Those giving informed consent will be screened using the criteria in box 1 and undergo baseline measurements and randomisation by a member of the research team via participant questionnaires and a detailed notes review (table 1).

**Table 1 T1:** Variables and schedule of data collection

No.	Variable	Data source		Schedule	
		Medical notes	Measured/collected at clinic	Baseline	Follow-up
1	Age		✓	✓	
2	Sex		✓	✓	
3	Ethnicity		✓	✓	
4	Marital status		✓	✓	
5	Education		✓	✓	
6	Duration of hypertension	✓		✓	
7	Past medical history	✓		✓	
8	Alcohol consumption		✓	✓	✓
9	Smoking		✓	✓	✓
10	Height		✓	✓	✓
11	Weight		✓	✓	✓
12	Clinic blood pressure (sitting and standing)		✓	✓	✓
13	Cholesterol (total and HDL)	✓		✓	
14	Estimated glomerular filtration rate	✓		✓	
15	Prescribed or over-the-counter medications (all medications)*	✓	✓	✓	✓
16	Quality of life (according to EQ-5D-5L)^26^		✓	✓	✓
17	Functional independence (defined by modified Rankin Scale)^38^		✓	✓	
18	Frailty (according to the FRAIL scale)^39^		✓	✓	✓
19	Frailty (according to the frailty index and electronic frailty index)^22 40^	✓	✓	✓	✓
20	Cognitive function (defined by the Montreal Cognitive Assessment)^41^		✓	✓	
21	Adherence to medication (according to the Medication Adherence Rating Scale Questionnaire)^42^		✓	✓	✓
22	Adherence to medication reduction		✓		✓
23	ICD-10 coded cardiovascular events and mortality during the trial	✓			✓
24	Recording of potential side effects to medication		✓	✓	✓
25	Recording of adverse events	✓	✓		✓

*Drug substance/name, formulation, dose, frequency, start date and adherence over past 12 months (according to clinical system).

HDL, high-density lipoprotein; ICD, International Statistical Classification of Diseases and Related Health Problems.

Blood pressure will be measured in a standardised fashion using the clinically validated^24^ BpTRU blood pressure monitor, which automatically records six blood pressure measurements at 1 min intervals. Blood pressure readings will be taken in the left arm (where appropriate) after participants have been seated for at least 5 min of rest, using an appropriate sized cuff. The mean of the second and third readings will be used to define the primary outcome. To test for orthostatic hypotension, two further readings will be taken in the standing position after 1 and 3 min.^25^ Only the research facilitator/nurse will be present during the blood pressure measurements. Orthostatic hypotension will be defined as a >20 mm Hg drop in systolic blood pressure within 3 min of standing.

All data will be collected via an electronic case report form (eCRF) linked to the study database. Participants will be given the option to enter responses to questionnaires themselves or with assistance from the research team. Where questionnaires are not validated for use on a tablet computer,^26^ or where individuals are not comfortable using one, paper copies will be made available for completion.

### Randomisation

Consenting participants will be individually randomised (1:1 allocation ratio) to one of two study arms using a fully validated web-based system (Sortition) with manual telephone back up. Participants will not be randomised until after consent has been taken and baseline assessments have been completed. A computer-generated non-deterministic algorithm, minimising on practice and baseline systolic blood pressure will be used to ensure these covariates are balanced between the two intervention arms.

The study will use an open-label design, so patients and practitioners will not be blinded to the intervention or study end points. Therefore, codebreaking will not be necessary. The statistical analysis will be performed blind to patient allocation.

### Intervention group

Participating GPs will review each participant’s antihypertensive medication regimen prior to the baseline appointment, and decide which medication should be removed if they are randomised to the intervention arm of the trial. The choice of medication to be withdrawn will be at the discretion of the GP, but their decision will be informed by an individual’s comorbidities and existing guidelines, where appropriate (figure 2). Specifically, participating GPs will be encouraged to identify previously unrecognised contraindications to medication, defined by the Screening Tool of Older Person’s Prescriptions (STOPP) criteria.^27^ In the absence of these, or a strong clinical rationale for continuing despite a STOPP criteria being met, GPs will be recommended to reduce antihypertensive medications in reverse of the National Institute for Health and Care Excellence C+A+D algorithm for older patients (figure 2).^23^ All participants in the trial will remain on at least one antihypertensive.

**Figure 2 F2:**
[figure not shown]
Medication reduction algorithm. Screening Tool of Older Person’s Prescriptions (STOPP) criteria withdraw one of the following medications if any of the ensuing contraindications are identified: thiazide diuretic with a history of gout (may exacerbate gout), beta-blocker in combination with verapamil (risk of symptomatic heart block), non-cardioselective beta-blocker with chronic obstructive pulmonary disease (risk of bronchospasm), calcium channel blockers with chronic constipation (may exacerbate constipation), use of diltiazem or verapamil with New York Heart Association class III or IV heart failure (may worsen heart failure). GP, general practitioner; NICE, National Institute for Health and Care Excellence.

Once a medication has been removed, GPs or other appropriate, delegated healthcare professionals will closely monitor the participant’s response to medication reduction: they will be given advice about what and when to monitor (figure 3), but this schedule will be flexible. All participants will be expected to return for at least one routine safety follow-up visit, and further visits may be required if blood pressure is raised (≥150 mm Hg), or AEs occur. Where blood pressure is persistently raised, GPs will be expected to re-adjust medication (dose or type), rendering the likelihood of an SAE occurring as a result of the intervention very low.

**Figure 3 F3:**
[figure not shown]
Postmedication reduction monitoring flow chart. The full effects of most oral antihypertensives can last for up to 4–6 weeks. Frequent monitoring in the initial 4 weeks after drug withdrawal is thus not required unless blood pressure (BP) levels are extreme or there are other clinical concerns (see above). Where systolic/diastolic BP values fall into different categories, consider the higher value. BP should be taken as the averaged second and third measurements using a validated monitor. Standard clinical care/monitoring should align with the National Institute for Health and Care Excellence recommendations.^23^

### Self-monitoring

All participants randomised to the medication reduction arm of the trial will be given the option to self-monitor their blood pressure at home. Those accepting will be trained using protocols developed in the previous TASMIN trials^28 29^ and will be given simple and clear instructions to contact their GP if their blood pressure rises above what is considered clinically safe (eg, *home* systolic blood pressure >145 mm Hg on all readings taken in a week). Participants will be advised to self-monitor (or have a carer monitor) at least four times per week in the last week of each month of follow-up (weeks 4, 8 and 12), although they can monitor more frequently if they wish. Differential use of self-monitoring in the intervention group, or indeed in the control group (many patients now self-monitor routinely)^30^ is not expected to impact on the study results, since there is good evidence that self-monitoring only affects blood pressure levels if used in combination with a co-intervention.^31^ All other clinical care will continue as usual.

### Control group

Those allocated to the control arm of the study will continue usual clinical care (ie, they will continue to take antihypertensive medications as prescribed and will not self-monitor unless already doing so). No other medication changes will be mandated and participating GPs will be asked to manage all other care according to usual clinical practice.

### Follow-up visits

Participants will attend one research follow-up clinic, 12 weeks (±2 weeks) after baseline and those in the intervention will attend one additional safety visit after 4 weeks (±2 weeks) (figure 1). A period of 4 weeks is expected to be sufficiently long enough to assess the impact of antihypertensive medication reduction, since these drugs usually take approximately 4 weeks to ‘wash out’ of a patient’s system. Earlier safety visits are not recommended since they could provide false reassurance that blood pressure is within safe limits if the withdrawn drug has not washed out of the participant’s system.

The follow-up assessments will include standardised blood pressure measurement (for assessment of the primary outcome), questionnaire assessments and adherence to the trial medication regime, side effects and AEs (table 1). Where possible, all participants will be flagged for mortality and hospital admissions using National Health Service patient tracking services, permitting long-term follow-up for up to 5 years after the trial has finished.

Each participant has the right to withdraw from the trial at any time. We will ask all participants to attend a follow-up visit as far as is practicable, regardless of whether medication is re-introduced to participants in the intervention group, or a participant in the control group has medication withdrawn. Unless a participant withdraws consent, vital status will be assessed even where an individual has been lost to follow-up (eg, moved away). If given, the reason for withdrawal will be recorded in the eCRF.

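### The ±2-week window lets the one required safety visit fall at week 2, although the same paragraph advises against visits before the roughly 4-week wash-out

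*Protocol article*

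**What the plan says.** In the protocol article, Follow-up visits gives the timing of the safety visit: "those in the intervention will attend one additional safety visit after 4 weeks (±2 weeks" either side. It justifies the 4-week target "since these drugs usually take approximately 4 weeks to" wash out, and then adds: "Earlier safety visits are not recommended since they could provide false reassurance that blood pressure is within safe limits". The research clinic follows at 12 weeks, also with a tolerance of 2 weeks either way.

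Three other places bear on the point:

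- **Intervention group** sets the minimum: "All participants will be expected to return for at least one routine safety follow-up visit". It makes anything beyond that conditional: "further visits may be required if blood pressure is raised (≥150 mm Hg), or AEs occur". On GP monitoring it says that "they will be given advice about what and when to monitor (figure 3), but this schedule will be flexible".
- **The Figure 3 legend** says: "The full effects of most oral antihypertensives can last for up to 4–6 weeks".
- **Self-monitoring** says that intervention participants "will be given the option to self-monitor their blood pressure at home". The suggested times are weeks 4, 8 and 12. The Figure 1 legend describes this as encouraged rather than required, and places the safety visit at 4 weeks without a tolerance.

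**The concern.** The window and its rationale pull in different directions at the lower edge. The reason given against early visits is that the withdrawn drug may still be acting, so a normal reading may not reflect the reduced regimen. That reason applies in weeks 2 and 3, which the window accepts.

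What is at stake is the safety check. The Intervention group section argues that serious harm from the intervention is very unlikely because GPs will re-adjust medication when blood pressure stays high. That argument depends on a reading taken once the drug effect has gone. A normal reading at week 2 meets the visit requirement, and because further visits are tied to raised pressure or adverse events, it triggers nothing more in the visible text. The primary outcome is measured at weeks 10 to 14, well after wash-out, so the main analysis is not touched.

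**Working it through.** The plan gives no figure of its own to reproduce. The check is interval arithmetic on the stated times.

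**Inputs**

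- Safety visit: 4 weeks ± 2 weeks, or day 28 ± 14 (Follow-up visits).
- Wash-out: about 4 weeks, or day 28 (Follow-up visits).
- Residual drug effect: up to 4–6 weeks, upper end day 42 (Figure 3 legend).
- Research clinic: 12 weeks ± 2 weeks, or day 84, range 70 to 98 (Follow-up visits).

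**Current window**

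- Limits: 28 − 14 = day 14 to 28 + 14 = day 42. Width: 42 − 14 = 28 days.
- Part before the stated wash-out: 28 − 14 = 14 days; 14/28 = 50% of the window.
- Wash-out time elapsed at the lower edge: 14/28 = 50%. Against the upper end in the Figure 3 legend: 14/42 = 33%.

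**Proposed window (4 weeks −3 days/+2 weeks)**

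- Limits: 28 − 3 = day 25 to day 42. Width: 42 − 25 = 17 days.
- Part before wash-out: 28 − 25 = 3 days. Elapsed at the lower edge: 25/28 = 89%.

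**Gap from the safety visit to the research clinic**

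| Safety visit on | To nominal day 84 | To earliest clinic, day 70 | To latest clinic, day 98 |
|---|---|---|---|
| Day 14 (current lower edge) | 84 − 14 = 70 | 70 − 14 = 56 | 98 − 14 = 84 |
| Day 25 (proposed lower edge) | 84 − 25 = 59 | 70 − 25 = 45 | 98 − 25 = 73 |
| Day 28 (on target) | 84 − 28 = 56 | 70 − 28 = 42 | 98 − 28 = 70 |

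A visit at the current lower edge therefore lengthens the gap by 70 − 56 = 14 days compared with an on-target visit. The proposed edge brings the longest gap to the nominal clinic down from 70 to 59 days. The upper edge, day 42, agrees with the rationale and needs no change.

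**Reading of the text.** The advice against earlier visits directly follows a sentence about a 4-week period, so it most naturally means before week 4. If it is read as before the window opens, the stated reason still applies to weeks 2 and 3. No visible text requires a repeat check when the visit takes place before week 4.

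**The case against.** The strongest reply is that a target with a tolerance is not a contradiction. Sites are told to aim for week 4 and not to plan earlier; ±2 weeks only says what still counts, and the 12-week clinic has the same tolerance. The advice is not a prohibition, and wash-out is only approximate. This is fair and keeps the point minor. But approximation covers a few days, not half of the stated wash-out period, and a symmetric tolerance has no support from a rationale that is one-sided.

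The second reply is that safeguards exist. GPs are to monitor closely, one visit is a floor rather than a cap, home monitoring is offered with training, and the Figure 3 legend warns GPs about lasting drug effects. The Figure 3 flow chart is not shown and may require further checks, and the article condenses a fuller protocol. These points limit how many participants could be affected. They do not remove the conflict: home monitoring can be declined, the monitoring schedule is flexible, and the visible legend says frequent monitoring in the first 4 weeks is unnecessary unless there is a particular concern.

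The third reply is that a day-25 visit is also early, and that even week 4 may precede full loss of effect for a drug lasting 6 weeks. Both are true. The change reduces the problem to a few days; it does not eliminate it.

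**Conclusion.** The concern holds as a minor internal conflict, confined to the lower edge of the safety-visit window. Half of the window (14 of 28 days) precedes the wash-out time that the protocol uses to justify the visit, and at the extreme the gap to the next scheduled clinic is 14 days longer than after an on-target visit.

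This rests on taking the approximate wash-out as day 28. The longer gap without a check also assumes a participant who has normal blood pressure at the early visit, declines home monitoring and receives no extra check through Figure 3 or the GP. The document does not say how many participants would be seen before week 4, so no share at risk can be given. Confidence is medium, mainly because Figure 3 is not visible.

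**What to change.** Set the safety visit at 4 weeks, −3 days/+2 weeks (days 25 to 42). The 3 days is an assumed value for a small scheduling tolerance, chosen because wash-out is approximate. Keep earlier visits available for symptoms or clinical concern, but do not count them as the routine safety visit. An alternative is to keep the present window and require a repeat blood pressure check at or after week 4 whenever the first visit falls earlier.

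The change is one line in the visit schedule and a notice to sites, through whatever amendment route the sponsor considers applicable, since the protocol is approved and recruitment had begun. The scheduling window narrows from 28 to 17 days, and some participants aged 80 or over who are seen before day 25 would need to attend again. Sample size, estimand and analysis stay as they are.
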